## Introduction

### Background and rationale {6a}

Postherpetic neuralgia (PHN) is the most common complication attributed to herpes zoster (HZ), which involves the reactivation of residual varicella zoster virus (VZV). Although the definition varies, pain that persists for 4 weeks to 6 months following acute HZ onset is recognized as PHN. Risk factors [1] for the development of PHN include older age, skin damage and pain intensity during acute HZ. In China, the prevalence of HZ is reported to be 7.7% [2] among the adult population, and an estimated 2.77 [3] million cases are diagnosed annually. Among those cases, 30% [2] are predicted to develop PHN after 12 weeks. Recent investigation [4] has shown that PHN is associated with sleep disturbances, lower quality of life, restricted daily activities and increased medical costs, all of which impose heavy burden on the patient and their finances. In addition, neuropathic pain [5] often persists for months or years and is refractory to drugs. Although a group of medications such as antidepressants, antiepileptics and topical agents are recommended by international guidelines, management of PHN is still challenging. Current therapeutic modalities fail to meet clinical expectations, as significant pain relief is achieved in less than 50% of patients [6] even with the most effective medications for PHN. Preventive and pre-emptive management [7] has been advocated for PHN in the future.

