### Sample size {14}

Based on the reported prevalence, the incidence of PHN in China is approximately 30% [2] after VZV reactivation. We predict that the same incidence will be observed in participants from the control arm. For participants in the duloxetine arm, the preventive protocol is expected to reduce the incidence to 20%. Assuming a 15% rate of loss to follow-up, a total of 750 participants would provide 90% power to detect the significant difference in the incidence of PHN using a 2-tailed alpha of 0.05.

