### Assignment of interventions: allocation

#### Sequence generation {16a}

After signing the written informed consent, participants will be randomized for allocation. Randomization will be performed using a web-based central randomization system with permuted blocks by an independent research assistant. Participants will be assigned to either the duloxetine arm or the control arm in an allocation ratio of 1:1. Given the open-label nature of this study, the patients, physicians and research team will inevitably be aware of the allocation. However, the outcome assessors will be blinded to the intervention.

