### Statistical methods

#### Statistical methods for primary and secondary outcomes {20a}

Statistical analyses will be performed using the SPSS 25.0 software package for Windows (SPSS, Inc., Chicago, IL, USA). The baseline and outcomes for the intervention will be compared to the control arm for primary analysis. Continuous variables will be expressed as the mean (SD) or median (IQR) and compared using Student’s *t* test or the Mann-Whitney *U* test. Normality will be tested using the Kolmogorov-Smirnov test. Categorical variables will be expressed as the number of patients (percentage) and compared using the chi-squared test or Fisher’s exact test. A 2-tailed alpha of 0.05 will be used as the threshold of statistical significance. The incidence of PHN in each arm at the end of week 12 will be compared using the chi-squared test. Subgroup analyses will be performed for age, gender, time to medication, maximum duloxetine dosage and average weekly pain score. Multiple logistic regression will be used to evaluate and determine the interference of the above confounding factors in the primary outcome. All analyses will be performed using both the intention-to-treat and per-protocol principles, and the final conclusion will be determined in line with the intention-to-treat principle.

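### The primary chi-squared test is valid but leaves unused the age and baseline pain that the plan names as PHN risk factors, and the planned regression gives no sound baseline-adjusted estimate

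*Protocol article*

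**What the plan says.** All references are to the protocol article.

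- **Primary test.** Statistical methods {20a}: "The incidence of PHN in each arm at the end of week 12 will be compared using the chi-squared test". No covariate is attached to it.
- **Known predictors.** Background and rationale {6a}: "Risk factors [1] for the development of PHN include older age, skin damage and pain intensity during acute HZ". Eligibility criteria {10} sets limits on age (over 50 years) and average pain (VAS at least 40 mm), so both have to be established before a participant is enrolled.
- **Planned adjusted model.** Sections {20a} and {20b} add subgroup analyses by age, gender, time to (or of) medication, maximum duloxetine dosage and average weekly pain score, and a multiple logistic regression of the primary outcome on the same factors. This regression is described as examining how those factors interfere with the primary outcome. It is not designated as the test of treatment.
- **Power.** Sample size {14} assumes PHN incidences of 30% and 20%, "using a 2-tailed alpha of 0.05". It states: "Assuming a 15% rate of loss to follow-up", "a total of 750 participants would provide 90% power".

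**The concern.** The plan identifies strong candidate predictors of its own outcome, holds two of them at baseline for every participant, and leaves them out of the analysis on which the conclusion rests. A prespecified adjustment for prognostic baseline variables usually sharpens the treatment comparison and corrects for chance imbalance in those variables. Both matter more in a trial whose power is below its stated level.

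The planned regression looks as if it might serve this purpose, so its contents need checking. If it conditions on consequences of treatment, its coefficient for arm cannot be read as the effect of duloxetine, and the reader is left with only the unadjusted comparison.

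**Working it through.** **1. The plan's own power figure.** Inputs from Sample size {14}: p1 = 0.30, p2 = 0.20, two-sided alpha 0.05, 750 enrolled 1:1, 15% lost. Evaluable: 750 × 0.85 = 637.5, about 319 per arm. Mean rate 0.25.

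Power = Φ{[0.10 × √319 − 1.96 × √(2 × 0.25 × 0.75)] / √(0.21 + 0.16)}
= Φ{(1.786 − 1.200) / 0.608} = Φ(0.963) = 83.2%.

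The stated 90% is not reproduced. It would need [(1.200 + 1.2816 × 0.608) / 0.10]² ≈ 392 per arm, which is 784 evaluable and 784 / 0.85 ≈ 923 enrolled. If all 750 were analysed, power would be 88.7%. At 90% power, 750 is approached only with a one-sided alpha of 0.05 (320 per arm, 640 / 0.85 ≈ 753), which contradicts the stated two-tailed alpha.

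**2. What adjustment could add.** The article gives no prognostic strength for age and baseline pain, so a range is assumed: one standardised baseline score combining them, with an odds ratio per SD from 1.0 to 3.5. For each value, 5,000 trials were simulated with 319 per arm and marginal incidences held at 30% and 20%. The uncorrected chi-squared test was compared with the Wald test for arm in a logistic model containing the score.

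| Assumed OR per SD | AUC | Chi-squared | Adjusted | Gain (points) |
|---|---|---|---|---|
| 1.00 | 0.50 | 82.7% | 82.6% | −0.1 |
| 1.35 | 0.58 | 83.7% | 83.9% | 0.2 |
| 1.65 | 0.63 | 83.8% | 84.9% | 1.1 |
| 2.12 | 0.69 | 83.3% | 86.2% | 2.9 |
| 2.72 | 0.74 | 84.1% | 88.5% | 4.4 |
| 3.49 | 0.79 | 83.1% | 90.0% | 6.9 |

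The simulation error of each power is about 0.5 point (√(0.83 × 0.17 / 5000) = 0.0053).

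**3. Cross-check by variance reduction.** If the covariates explain a share R² of outcome variance, the effective size per arm is about 319 / (1 − R²). The formula in step 1 then gives 83.2% at R² = 0, 85.1% at 0.05, 86.9% at 0.10 and 90.5% at 0.20. These R² values correspond roughly to odds ratios per SD of 1.65, 2.1 and 3.5, so the two methods agree to within about a point.

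**4. Whether the planned regression already does this.**

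| Factor | Status |
|---|---|
| Age, gender | Baseline |
| Time to medication | At or near entry, on a plain reading |
| Maximum duloxetine dosage | After randomisation: under Intervention description {11a}, controls receive none, and in the duloxetine arm the dose rises when VAS has not reached 0. It carries both arm and response. |
| Average weekly pain score | After randomisation: it is itself a secondary outcome, on the scale that defines PHN. |
| Baseline VAS | Not named |

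Conditioning on the third and fourth factors removes or distorts part of the effect being estimated.

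**The case against.** The strongest reply is that nothing here is an error. An unadjusted chi-squared test is valid in a 1:1 randomised trial and matches the comparison of two incidences on which the sample size rests, so an adjusted primary model is a preference about efficiency. This stands as a limit on the point, and a reader should not infer that the primary test is wrong.

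Second, the plan does contain an adjusted model, and it includes age. This also stands. It would be unfair to say that the plan adjusts only for post-randomisation variables or ignores age altogether. But the model is not the deciding analysis, omits baseline VAS, and mixes in two variables that follow treatment.

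Third, the gain is assumed. Entry limits on age and pain may narrow the range of both covariates and weaken them as predictors, and the top of the range needs an AUC near 0.79. That is a fair reason to expect the lower part of the range. It is no reason to avoid adjustment, since the simulation shows no loss beyond its error when the score has no prognostic value.

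Two stronger readings are tempting and are not supported:

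- **That allocation is unstratified.** Sequence generation {16a} says only: "Randomization will be performed using a web-based central randomization system with permuted blocks". A condensed article may leave stratification factors to the full protocol, so this silence shows nothing.
- **That adjusting for centre would gain power.** The trial has 18 centres, but no section calls centre prognostic, so no such gain can be derived.

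**Conclusion.** The point holds as a loss of efficiency in the primary analysis, together with a planned regression that cannot serve as the baseline-adjusted estimate of the treatment effect. The size is a gain of roughly 0 to 7 points over about 83% power, and about 1 to 3 points for modestly prognostic covariates (odds ratio about 1.65 to 2.1 per SD). It rests on the plan's incidences and loss rate, equal loss in both arms, and an assumed prognostic strength. The simulation tested the logistic coefficient for arm; a test on the standardised risk difference was not simulated separately, though the variance-reduction check points to the same size.

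A reader might infer that adjustment restores the stated 90%. Only the strongest scenario reaches it. The shortfall comes from the sample-size calculation and has to be corrected there.

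**What to change.** 1. Make the primary analysis a prespecified logistic model with arm, baseline VAS and age, the last two as continuous variables. Report it as a standardised risk difference with 95% CI, which keeps the result on the scale of the sample-size assumption. State which test from this model decides the primary hypothesis.
2. Keep the chi-squared test as a sensitivity analysis.
3. Leave maximum duloxetine dosage and average weekly pain score out of any adjusted model for the treatment effect.
4. If an expected gain in power is quoted, label it as an assumption. Correct the 90% statement in Sample size {14} separately.

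Skin damage is also a named risk factor, but the text shown describes no baseline measure of it, so it is not part of this proposal.

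The cost is a change of wording in the analysis plan, made before outcome data are examined, and a little more analysis work. No additional data item or participant is needed. The small downside is reliance on a model for the primary result, which the retained chi-squared test lets readers check.

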#### Interim analyses {21b}

Any AE or SAE (serious adverse events) will be reported to the DSMB and the IRB (Institutional Review Board) for judgement. Anticipated severe problems that may be detrimental to the participants include rapid-onset hyponatremia, delirium, haemodynamic instability. The aforementioned adverse events and other serious life-threatening adverse events leading to prolonged hospital stay or death will be reported to the IRB of the respective participating centre, and our study will be terminated immediately.

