### Additional consent provisions for collection and use of participant data and biological specimens {26b}

The consent form will include the permission of collection and use of participant data, should the participants decide to withdraw from the trial, along with the permission to share relevant data with members of regulatory authorities, when necessary. This trial does not involve the collection of biological specimens.

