### Strategies to improve adherence to interventions {11c}

Once assigned to one of the two study groups, a pharmacological protocol will be given as per allocation. Physicians and research assistants will be responsible for instructing participants to follow the protocols correctly, and to ensure adherence to interventions. After recruitment, each participant will be given a pain diary (PD), in which all outcomes can be recorded by the participants themselves during the study period. The specific recording criteria are as follows: (i) the VAS score will be recorded every morning before breakfast, (ii) AEs and consumption of each analgesic will be recorded every evening before bed, and (iii) the 12-item Short-Form Health Survey (SF-12), Patient Global Impression of Change Scale (PGIC) and Sleep quality as measured by the Pittsburgh Sleep Quality Index (PSQI) will be self-assessed at baseline and upon completion of weeks 4, 8, and 12. During the study period, the research assistants will monitor the participants’ completion of the PDs and deliver reminders as necessary through telephone calls or social media. At the end of week 12, the PDs will be collected by the research assistants and stored by the Data Safety Monitoring Board (DSMB). The research assistants will be available 24 h a day, 7 days a week, to answer any questions related to the study.

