### Provisions for post-trial care {30}

Hyponatremia, delirium and haemodynamic instability during the study period are anticipated for the participants of this trial.

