### Data collection and management

#### Plans for assessment and collection of outcomes {18a}

Research assistants will gather the patients’ baseline demographic characteristics searching the institutional electronic medical records or asking participants directly. The baseline and outcomes for the intervention will be compared to the control arm for primary analysis. After recruitment, each participant will be given a PD, in which all outcomes can be recorded by the participants themselves during the study period. The specific recording criteria are as follows: (i) the VAS score will be recorded every morning before breakfast, (ii) AEs and consumption of each analgesic will be recorded every evening before bed, and (iii) the SF-12, PGIC and PSQI will be self-administered at baseline and upon completion of weeks 4, 8 and 12. During the study period, the research assistants will monitor the participants’ completion of the PDs and deliver reminders as necessary through telephone calls or social media software. At the end of week 12, the PDs will be collected by the research assistants and stored by the DSMB. An investigator will sample every participant file and check for missing data.

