## Discussion

This is a large randomized, multicentric, open-label, blinded-endpoint study aiming to test whether premedication with duloxetine within 72 h after VZV reactivation has a preventive effect against PHN. To the best of our knowledge, this study is the first to examine the preventive effects of duloxetine on PHN. PHN is the most common complication following acute HZ. Based on recent epidemiological studies, 61.8% to more than 70% of PHN cases in China develop in patients aged more than 50 years [3, 4]. The results of these studies were consistent with previous findings in western countries [6]. Patients older than 50 years have long been the main subjects for studies on PHN in prior clinical trials [19, 21]. For a pragmatic study design, only patients aged more than 50 years will be included in the present study. Duloxetine, a serotonin–norepinephrine reuptake inhibitor, was first approved for primary depression. In recent years, it has also been recommended as the first-line [24] therapy for neuropathic pain. The recommended usage of oral duloxetine is to start at 30 mg once a day and gradually increase by 30 mg each time until the optimal dosage. An alternative usage is to begin at 20 mg and increase by 20 mg each time until optimal dosage. In this study, the latter is chosen for its superior accuracy. The maximum dosage of duloxetine allowed is 120 mg per day. In the treatment of diabetic neuropathy and fibromyalgia, a higher dosage of duloxetine demonstrated no benefit compared to 60 mg per day and was not tolerated as well as the lower dose. On the other hand, pharmacodynamically, duloxetine inhibits the uptake of both serotonin and norepinephrine, of which the former is inhibited much more strongly than the latter. One study suggests that the inhibition of norepinephrine (NE) [31] is relatively weak if the daily oral dose of duloxetine is less than 60 mg. In our study, patients aged more than 50 years will be recruited. Hence, considering the safety issues and pharmacodynamic effectiveness, 60 mg per day will be set as the maximum dosage. Long-term tolerance has been proven by a previous study, in which duloxetine was administered at 60 mg twice per day for 52 [32] consecutive weeks. No severe drug-related side effects or AEs were observed. Notably, duloxetine was found with rapid-onset hyponatremia and delirium, according to a recent investigation [33]. Concerning events will be carefully monitored throughout the study period. Regarding drug interactions, duloxetine is not documented to be a contraindication to valacyclovir or vice versa. Similarly, based on our pilot study, no specific adverse events were observed for duloxetine in combination with valacyclovir, and no drug interactions were detected. During the study period, the principal investigators will monitor all AEs and SAEs in real time. The safety precautions in our study will be further adjusted based on the study process and AE reports.

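### The three severe harms tied to study termination have no stated method of detection beyond a participant-written diary, so they may be under-recorded and detected unequally between arms

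*Protocol article*

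**What the plan says.** **Harms named.** Interim analyses {21b} states: "Anticipated severe problems that may be detrimental to the participants include rapid-onset hyponatremia, delirium, haemodynamic instability". Provisions for post-trial care {30} repeats the list: "Hyponatremia, delirium and haemodynamic instability during the study period are anticipated for the participants of this trial". Adverse event reporting and harms {22} names the same three. Both {21b} and {22} attach reporting to the review board and termination of the study to events of this kind.

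**How adverse events are recorded.** Under Plans for assessment and collection of outcomes {18a}, "each participant will be given a PD, in which all outcomes can be recorded by the participants themselves during the study period". Strategies to improve adherence {11c} gives the schedule: "AEs and consumption of each analgesic will be recorded every evening before bed". Until the diaries are handed in, research assistants check that they are being completed and send reminders by telephone or social media. Then, "At the end of week 12, the PDs will be collected by the research assistants".

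**Other monitoring.** After mentioning hyponatremia and delirium with duloxetine, the Discussion says "Concerning events will be carefully monitored throughout the study period". It also has the principal investigators following adverse events as they arise. Section {11b} promises close monitoring and full documentation. Sections {5d} and {21a} give safety review to the steering committee and the data monitoring committee. None of these sections says how a case would be found.

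**Specimens.** Additional consent provisions {26b} says "This trial does not involve the collection of biological specimens". The parallel statement in {33} is confined to genetic or molecular analysis for future use.

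**The concern.** Each of the three harms is poorly suited to self-report. Hyponatremia is a laboratory finding. A person with delirium cannot be relied on to record it. Haemodynamic instability generally has to be measured. Yet these are the events the article singles out as serious enough to end the trial.

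Two consequences follow if detection is left to the diary and to whatever usual care happens to diagnose. First, counts in both arms may be too low, and the committees can review only what reaches them. Second, participants and physicians know the allocation and the article itself links duloxetine to hyponatremia and delirium, so testing and questioning may be more frequent in that arm. The between-arm comparison of adverse events, which the Abstract lists among the secondary outcomes, would then partly reflect how hard people looked. The primary analysis of postherpetic neuralgia is not affected.

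**Working it through.** The plan gives no figure on this point, so there is nothing to reproduce. The check is a comparison of passages, followed by an illustration.

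**Step 1: each harm against the recording method.**

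| Harm | What identifying it generally needs | What the article describes |
|---|---|---|
| Rapid-onset hyponatremia | Serum sodium result | Evening diary; no sodium test mentioned |
| Delirium | An observer or an assessment | Evening diary written by the affected person |
| Haemodynamic instability | Blood pressure and pulse readings | Evening diary; no vital-sign schedule mentioned |

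**Step 2: whether the other monitoring fills the gap.** Sections {11b}, {5d}, {21a} and the Discussion say who watches and who reviews. They do not say how a case enters the data. Severe cases that reach clinical care could be reported by that route; milder or untested cases might not be.

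**Step 3: illustration of under-recording.** Inputs: 750 participants (Sample size {14}) allocated 1:1 (Trial design {8}), so 750 / 2 = 375 per arm. The share *s* of true cases recorded is not in the document and is assumed over a range.

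- Upper bound on true risk after zero recorded events (one-sided 95%): (1 − 0.05^(1/375)) / *s* = 0.796% / *s*.
- Chance of recording no event when the true risk is *p*: (1 − *p·s*)^375, shown for an assumed *p* of 1%.

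| Assumed *s* | Upper bound | Chance of no recorded event, *p* = 1% |
|---|---|---|
| 100% | 0.80% | 2% |
| 50% | 1.6% | 15% |
| 25% | 3.2% | 39% |
| 10% | 8.0% | 69% |

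At an assumed true risk of 3% and *s* = 10%, 375 × 0.03 = 11.3 true cases would yield 11.3 × 0.10 = 1.1 recorded cases on average, and none at all with probability (1 − 0.003)^375 = 0.32.

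If the 15% loss to follow-up in {14} removes participants from the safety count, about 318 remain per arm. The bounds become 0.94%, 1.9%, 3.8% and 9.4%.

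**Step 4: illustration of unequal detection.** The recorded risk ratio equals the true ratio multiplied by *s* on duloxetine over *s* in control. With assumed shares of 30% and 15% and equal true risks of 3%, the expected recorded cases are 375 × 0.03 × 0.30 = 3.4 and 375 × 0.03 × 0.15 = 1.7, a ratio of 2. That ratio is simply the assumed 30/15. It shows the mechanism and is not an estimate.

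**The case against.** The strongest reply is that this is a condensed article. It refers to protocol version 1.1 and to an operation manual and forms, and a schedule of safety tests could sit in any of them. That stands, and it is why the point concerns the method of detection as published and does not assert that no testing takes place. Several stronger readings are tempting and should be resisted.

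- A reader might infer from {26b} that no sodium can ever be measured. That sentence is unqualified, but it sits under a consent heading and {33} is limited to genetic or molecular work. Neither expressly excludes clinical safety blood tests.
- A reader might infer that the trial cannot detect these events at all. The investigator and committee monitoring in {11b}, {5d}, {21a} and the Discussion, and the contacts by research assistants, mean that severe cases reaching care could still be reported.
- A reader might take the abbreviation list under Table 1 as evidence that no laboratory or vital-sign item is scheduled. The table itself is not available in the text reviewed, and a list of abbreviations is not a list of assessments.
- A reader might say a low count will be presented as proof of safety. The article says no such thing, and no safety margin or decision rule rests on a zero count. It is a risk of interpretation only.

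It is also fair to object that every detection share above is assumed. The arithmetic shows how much depends on detection; it does not show what detection will be.

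What the reply does not remove is the mismatch within the published text: a specified self-report instrument, harms unsuited to self-report, termination tied to those harms, and monitoring promised without a method.

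**Conclusion.** The concern holds in a limited form. The article names three severe harms, ties study termination to them, and describes only a participant diary for recording adverse events. A diary cannot reliably detect them, and the further monitoring has no stated method. Under-recording in both arms and unequal detection between arms are therefore plausible, the latter because the trial is open-label. Neither can be sized from the document. Under assumed detection of 100% down to 10%, the upper bound after zero events in 375 participants runs from 0.8% to 8.0%.

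This should be addressed, with medium confidence. If the full protocol already schedules the relevant measurements, the reconciliation reduces to a clarifying sentence, though equal questioning and reporting of numbers tested would remain useful.

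**What to change.** 1. Reconcile {26b} and {33} with {11b}, {21b}, {22} and the Discussion, stating whether any safety blood test or vital-sign measurement is done. Which measurements or clinical rules are right is for the sponsor to settle.
2. In the telephone or social-media contacts already planned, ask both arms the same short fixed questions on confusion, fainting, falls and hospital contact, and accept a household member's answer.
3. At week 12, extract from the centre's records, on one form for both arms, any sodium result, admission or emergency visit. Section {18a} already describes use of institutional records at baseline: "Research assistants will gather the patients’ baseline demographic characteristics searching the institutional electronic medical records or asking participants directly".
4. Report hyponatremia with the number tested in each arm. If sodium is not measured systematically, do not take a zero or low count as evidence of absence.

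**Cost.** Research-assistant time and a more cautious safety statement; items 2 to 4 call for no added visit or specimen. The extraction is not trivial: 750 participants over 18 centres is about 42 per centre. The access described in {18a} covers baseline demographics only, and Confidentiality {27} restricts personal files to each centre's lead investigator, so access for this purpose has to be arranged.

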### Criteria for discontinuing or modifying allocated interventions {11b}

All the AEs (adverse events) of the study will be closely monitored, properly documented in detail, and reported to the ethics committee with the aims of resolving the condition or even dissolution of the study if necessary.

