### Oversight and monitoring

#### Composition of the coordinating centre and trial steering committee {5d}

The coordinating centre (CC) will be responsible for the training of all research assistants and the coordination of all standardized quality control aspects such as PDs, operation manual and forms. It will include a Principal Investigator (PI), two expert pain management specialists, a pain management nurse and a statistician. It will serve as a link between all the 18 centres involved in the study, the research assistants involved in recruitment, assistance and follow-up.

The trial steering committee (TSC) will include the PI, an independent chair, two independent pain physicians and an independent statistician. It will supervise the trial progress, resolve unanticipated complications if any and assess AE and SAE and their potential correlation with the study drugs. It will supervise the work of various subcommittees such as quality control subcommittee for the training of research assistants, subcommittee of research assistants involved in recruitment and clinical activities, subcommittee for publications and presentations at the completion of the study. The TSC will report any unforeseen events and report to the IRB. The IRB of Beijing Tiantan Hospital will be supervising the trial and meet at least annually to oversee the study conduct and progress.

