#### Composition of the data monitoring committee, its role and reporting structure {21a}

The data monitoring committee (DMC) comprised of two statisticians and a pain physician will perform independent review of data outcomes and patient safety. It will meet biannually and report to the TSC.

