#### Adverse event reporting and harms {22}

The TSC will conduct regular inspections of the trial progress and report any unforeseen events to the IRB. Any AE or SAE (serious adverse events) will be reported to the IRB (Institutional Review Board) for judgement. Anticipated severe problems that may be detrimental to the participants involve rapid-onset hyponatremia, delirium and haemodynamic instability. Such serious life-threatening adverse events as well as other severe complications leading to prolonged hospital stay or death will be reported to the IRB and our study will be terminated immediately.

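### The protocol orders immediate termination of the whole study on serious events it also sends for judgement, with no count, arm, causality condition or deciding body

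*Protocol article*

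**What the plan says.** Two sections of the protocol article state the rule. Interim analyses {21b} lists rapid-onset hyponatremia, delirium and haemodynamic instability. It says these, and other serious life-threatening events that prolong hospital stay or cause death, "will be reported to the IRB of the respective participating centre, and our study will be terminated immediately". Adverse event reporting and harms {22} refers to the same three problems as serious life-threatening events, adds other severe complications, and continues: "leading to prolonged hospital stay or death will be reported to the IRB and our study will be terminated immediately".

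Other statements bear on the same decision:

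- {21b}, opening sentence: "Any AE or SAE (serious adverse events) will be reported to the DSMB and the IRB (Institutional Review Board) for judgement".
- {22}, second sentence: "Any AE or SAE (serious adverse events) will be reported to the IRB (Institutional Review Board) for judgement".
- Criteria for discontinuing or modifying allocated interventions {11b}: adverse events are "reported to the ethics committee with the aims of resolving the condition or even dissolution of the study if necessary".
- Provisions for post-trial care {30}: "Hyponatremia, delirium and haemodynamic instability during the study period are anticipated for the participants of this trial".
- Trial steering committee {5d}: the TSC is to "assess AE and SAE and their potential correlation with the study drugs".
- Data monitoring committee {21a}: the DMC "will perform independent review of data outcomes and patient safety", meeting biannually and reporting to the TSC.

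**The concern.** The termination sentences carry no condition. They do not say how many events are needed, in which arm, whether the event must be related to duloxetine, or who decides. The wording is plural but gives no count, so on a literal reading a single event in either arm is enough. That could be a death unrelated to study drug in a control participant, in a population aged over 50.

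This does not fit with the rest of the article. An immediate stop leaves nothing for the DSMB or IRB to judge. {11b} treats dissolution as a step taken only when needed. The TSC's causality assessment and the DMC's safety review exist but are not connected to the stop. {30} describes hyponatremia, delirium and haemodynamic instability as anticipated, so the stop is tied to kinds of event the investigators foresee.

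If the rule is followed, the trial may end early for a reason that says nothing about duloxetine. If it is not followed, the investigators depart from their approved protocol. Whether to stop, and on whose decision, is then settled only once an event has occurred, in an open-label trial.

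**Working it through.** **The plan's own figures.** The stopping rule has none to reproduce. The relevant design inputs come from Sample size {14} and Trial design {8}: 750 participants, 1:1 allocation, 30% versus 20%, two-sided alpha 0.05, 15% loss. The stated power is 90%. With 750 × 0.85 / 2 ≈ 319 evaluable per arm, the pooled two-proportion z test gives

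- null standard error √(2 × 0.25 × 0.75 / 319) = 0.0343; alternative standard error √((0.21 + 0.16) / 319) = 0.0341
- power = Φ((0.10 − 1.96 × 0.0343) / 0.0341) = Φ(0.96) ≈ 83%.

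The gap between 83% and the stated 90% is a separate matter. I use 83% as the comparator so that all power figures below are computed the same way.

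**Chance that the rule stops the trial.** The documents give no event rate, so the 12-week risk q of a qualifying event per participant is an assumption, shown over a range.

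- At least one event: 1 − (1 − q)^n, with n = 750 (either arm) or n = 375 (duloxetine arm only).
- At least two events: 1 − (1 − q)^750 − 750q(1 − q)^749.

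| Assumed q | One event, either arm | One event, duloxetine arm only | Two events, either arm |
|---|---|---|---|
| 0.01% | 7% | 4% | 0.3% |
| 0.05% | 31% | 17% | 5% |
| 0.1% | 53% | 31% | 17% |
| 0.2% | 78% | 53% | 44% |
| 0.5% | 98% | 85% | 89% |

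For an even chance of reaching 750 under the single-event reading, q must be at most 1 − 0.5^(1/750) ≈ 0.092%.

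**Power at the median stop (single event, either arm).** Study setting {9} expects about 3 years of recruitment. I assume even accrual over 156.5 weeks (750 / 156.5 = 4.79 per week, about 57 per 12 weeks) and an event time uniform over each participant's 12 weeks. The median stop is the time t at which the product over participants of 1 − q × min(1, max(0, (t − entry) / 12)) equals 0.5. Evaluable per arm is the number who completed 12 weeks × 0.85 / 2.

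| Assumed q | Median stop (week) | Enrolled | Completed 12 weeks | Evaluable per arm | Power |
|---|---|---|---|---|---|
| 0.1% | 150.6 | 722 | 664 | 282 | 78% |
| 0.2% | 78.2 | 375 | 317 | 135 | 47% |
| 0.5% | 34.9 | 167 | 110 | 47 | 20% |

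If everyone enrolled at the stop were still followed to week 12, the evaluable number becomes enrolled × 0.85 / 2 and power is about 82%, 54% and 28%. Below q ≈ 0.092% the median stop is not reached.

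**The case against.** The strongest defence reads the sections in sequence: events are reported, the DSMB and IRB judge them, the TSC considers causality, and the trial stops only if warranted. The Discussion supports this by saying that safety precautions will be adjusted in the light of adverse event reports, which presumes that the trial continues. Section {22} can also be read as limiting the three named problems to life-threatening cases. Anticipated may mean no more than foreseeable, and {30} names plain hyponatremia where the stopping text names the rapid-onset form. Counts and thresholds normally belong in the full protocol or DMC charter. The stopping probabilities rest wholly on assumed risks, and the rule errs toward participant safety.

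Much of this is fair and trims the point. {30} is secondary support. The probabilities show sensitivity to the assumed risk and do not estimate what will happen. Leaving numerical thresholds to a charter is no fault. It is also true that any discretionary review, including the one proposed here, takes place after an event; what the text lacks is a named body and process fixed beforehand.

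The central conflict stands. The sequential reading needs a condition that neither termination sentence contains. The restriction to life-threatening cases adds no arm, causality or decision-maker, and {22} still includes other severe complications that prolong hospital stay. If stopping treatment in the individual was meant, the text says something else, because both sections refer to the study.

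**Conclusion.** The point holds: the rule is wrong as written. The article states an unconditional termination rule twice, and that rule contradicts the judgement step in the same sections and the conditional wording of {11b}. It is a stated rule that would harm the trial if followed, so it cannot be put down to detail left out of a condensed article.

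Its size depends on an event risk that the documents do not give. Under the single-event reading the typical power loss is small at 0.1% per participant or below (78% or more, against 83%) and large from about 0.2% (47%). These figures also assume even accrual, uniform event times, 15% loss and analysis of those who completed 12 weeks. Reading the plural as two events, or counting only the duloxetine arm, lowers the chance of stopping but leaves the contradiction in place. It should be fixed. The sample size, endpoint and analysis are not affected.

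**What to change.** Delete the immediate-termination clause from {21b} and {22}. In both places state that:

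- the listed events are reported on an expedited basis;
- study drug is stopped in the affected participant where appropriate;
- any decision to pause or stop the trial is made on prompt DMC review and the TSC's causality assessment, and is reported to the IRB.

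The text should say that this review is unscheduled and prompt, because {21a} provides only for biannual DMC meetings. The wording then agrees with the judgement step in {21b} and {22} and with the conditional dissolution in {11b}. Numerical thresholds can stay in the full protocol or DMC charter.

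The cost is a short amendment to two sentences, a clause allowing unscheduled DMC review, and IRB approval. Both committees already exist.
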